#### Non-inferiority evaluation

2.9.2

Differences between the study-arms with 95% confidence interval and p-values will be calculated for the crude and adjusted models based on potential differences in patient characteristics with a non-inferiority margin of three points on the NDI over 12 months. Missing data and reasons for drop-outs will be reported. Linear/logistic mixed models handle missing data more flexibly due to its reliance on maximum likelihood estimation, which allows for the incorporation of missing values under missing at random assumptions.

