#### Randomisation and blinding

2.3.2

After baseline measurement, an in independent researcher randomly allocates participants via a phone call to personalised multimodal physiotherapy or surgery with a 1:1 allocation ratio using concealed, computer-generated block randomisation (block sizes of four or six) [26]. Due to the nature of the study, blinding of patients and health care providers is not feasible. However, the clinical investigators and the statistician conducting the analyses are blinded.

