#### Follow-up time-points

2.3.4

Follow-up assessments will take place at three, six, and 12 months. To reduce the risk of recall bias in cost reporting, an additional cost evaluation will be conducted at nine months. Participants who have not completed the follow-up questionnaire will receive reminders on days five and eight. If responses are still missing after two weeks, a follow-up phone call will be made to encourage adherence to the study.

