### Sample size and non-inferiority margin

2.6

A sample size of 126 participants is needed to achieve a power of 0.80 to test the hypothesis that personalised multimodal physiotherapy is non-inferior to ACDF surgery, with a standard deviation of six points on the NDI, an alpha of 2.5%, and allowing for a drop-out rate of up to 20% [48,49].

To determine the non-inferiority margin, we calculated the Smallest Worthwhile Effect (SWE) for the Neck Disability Index (NDI). The SWE represents the minimum clinical benefit required to justify a treatment, accounting for its specific risks, costs, and burdens [50,51]. While a 20% between-group difference is typically recommended for conservative treatments [50], this threshold is often increased by 10% for chronic conditions [52].

In consultation with our patient representative, we set the SWE at 30%. Given that the Minimal Clinically Important Change (MCIC) for patients undergoing surgery for cervical radiculopathy is nine points on the NDI [53], the 30% threshold translates to 3 points non-inferiority margin. Consequently, physiotherapy is considered non-inferior to surgery if the difference in NDI improvement between the two groups is less than three points.

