#### Statistical analysis

2.9.1

First, normality of the data will be checked by the Kolmogorov-Smirnov test and visual inspection of Q-Q plots, box plots, and histograms. If needed, data will be transformed to obtain normal residuals. The primary analysis will be conducted according to the intention-to-treat principle, with secondary analyses performed based on the per-protocol approach. A one-sided alpha of 2.5% will be used. For the primary and secondary outcomes, linear mixed models will assess between-group differences in outcome measures over 12 months. To analyse the over-time effect, the fixed part of the model will include the outcome measure over time, treatment group, and baseline outcome correction (when applicable). A random intercept will be selected to account for the correlated nature of multiple measurements from the same participant. Potential confounders will be included as covariates in the adjusted model. To assess the differences in treatment effect at each time point, we will include an interaction term between time and treatment group. The regression coefficient (B), p-value, and confidence intervals (95% CI) will be computed for the crude models (only corrected for the baseline value of the outcome) and the confounder-adjusted models.

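### The NDI analysis rests on missing at random alone, and the final follow-up call is not said to collect the NDI; completing the NDI on that call is a cheap safeguard

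*Protocol article*

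**What the plan says.** Section 2.9.2 (Non-inferiority evaluation) analyses the NDI with mixed models fitted by maximum likelihood, "which allows for the incorporation of missing values under missing at random assumptions". It adds: "Missing data and reasons for drop-outs will be reported". No analytic use of those reasons is described. Section 2.9.1 makes intention-to-treat primary and per-protocol secondary, and corrects for the baseline value of the outcome.

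Section 2.3.4 (Follow-up time-points) fixes the retrieval procedure. Reminders go out on days five and eight, and then: "If responses are still missing after two weeks, a follow-up phone call will be made to encourage adherence to the study". The section does not say whether the NDI is completed on that call.

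Four other statements bear on the point:

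- Section 2.6 describes the sample size as "allowing for a drop-out rate of up to 20" per cent.
- Section 2.3.2 says that "blinding of patients and health care providers is not feasible", and section 2.5.1 describes the NDI as self-reported.
- Section 2.4.1 gives physiotherapy a course of eight to 12 weeks.
- Table 1 places the NDI at baseline and at 3, 6 and 12 months.

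**The concern.** Missing at random lets the model predict an absent NDI from what was recorded for that patient and for similar patients. It fails when the chance of being missing depends on the unseen value itself.

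The timing makes this most plausible early on. The first follow-up NDI comes at about the time the physiotherapy course ends. A patient lost during treatment because of a poor course has no recorded NDI reflecting that course. With baseline NDI as a covariate and not as an outcome, that patient also supplies no outcome row to the model, although the analysis is called intention-to-treat. The per-protocol analysis does not test the assumption.

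The direction matters in a non-inferiority trial. If the missing physiotherapy patients are worse than predicted, and the missing surgery patients are not equally so, the estimated difference is too small and the error favours the claim. An NDI value that was never collected cannot be restored by any analysis plan written later.

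**Working it through.** **1. The plan's own sample size.** The inputs from section 2.6 are SD 6, margin 3, alpha 2.5% (one-sided, section 2.9.1) and power 0.80. No numerical true difference is given, so I assume 0.

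n per arm = 2 × (1.960 + 0.842)² × 6² / 3² = 62.8, rounded up to 63, or 126 in total.

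This matches the stated 126 before any drop-out. With 20% drop-out, 63 / 0.8 = 78.75, rounded up to 79 per arm, or 158. That mismatch is a separate matter. Here it means only that 20% loss from 126 leaves 126 × 0.8 = 100.8 patients, or 50.4 per arm.

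**2. Room below the margin after 20% loss.** Count a positive difference as worse for physiotherapy.

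- SE = 6 × √(2 / 50.4) = 1.195
- 95% half-width = 1.96 × 1.195 = 2.34
- Largest estimate that still passes = 3 − 2.34 = 0.66

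**3. Bias.** Let m be the share of an arm that is missing, and d the mean amount by which its unseen NDI exceeds the model's prediction.

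Understatement of the difference = m(physio) × d(physio) − m(surgery) × d(surgery).

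Equal products give 0. With no shift in surgery, the understatement is m × d, even if the two arms lose the same share.

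**4. Shift that brings the upper limit to 3 from an observed difference of 0.** Solve m × d = 0.657, holding the SE at 1.195. Here m is the share of the physiotherapy arm that is both missing and shifted.

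| m | d (NDI points) |
|---|---|
| 20% | 3.3 |
| 15% | 4.4 |
| 10% | 6.6 |
| 5% | 13.1 |

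For the point estimate itself to reach 3 at m = 20%, d must be 3 / 0.20 = 15.

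**5. Chance of a false non-inferiority claim when the true difference is 3 (nominal 2.5%).** The formula is Φ(−1.96 + m × d / 1.195).

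| m | d = 3 | d = 6 | d = 9 |
|---|---|---|---|
| 20% | 7.2% | 17.0% | 32.5% |
| 5% | 3.3% | 4.4% | 5.7% |

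The shifts are assumptions. Nine points is the minimal clinically important change quoted in section 2.6, used here only as a scale.

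**6. Gain from retrieval.** If the call recovers half of a 20% loss, evaluable patients rise from 100.8 to 126 × 0.9 = 113.4. The SE ratio is √(100.8 / 113.4) = 0.943, a fall of about 6%.

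**The case against.** The case on the other side is substantial, and much of it stands.

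- A mixed model under missing at random is a conventional primary analysis, and the article contradicts nothing by stating it. Delta-shift or tipping-point analyses are commonly left to an analysis plan, which is not shown. That none appears in the article is therefore not a defect.
- A reader might infer that the call collects no NDI and that a reachable non-responder stays missing. Section 2.3.4 is silent on this, and a call that prompts someone to finish the online survey would also recover the NDI.
- A reader might infer that symptoms or preference drive patients out of the study. The symptom-driven rules in section 2.4.3 concern treatment: delayed surgery, or surgery cancelled on remission. Intention-to-treat can still use those patients' NDI. Having delayed surgery available within the study may even weaken the motive to withdraw. The article does not say what drives study drop-out.
- Drop-out that depends on NDI already recorded at baseline, 3 or 6 months is covered by missing at random.
- The 20% is an overall planning ceiling. Applying it as complete loss, with the shift in one arm only, is upper-end, because patients with some visits still contribute. Selection could also run the other way.

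The operational point survives these objections. The article does describe the retrieval step, and the only purpose it gives for the last contact is encouragement.

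**Conclusion.** This is a cheap improvement to a stated procedure and not an error in the analysis. For the NDI the article states missing at random alone, and it does not say that its last contact collects the outcome. A bias towards non-inferiority arises only if unobserved physiotherapy patients fare worse against prediction than unobserved surgery patients, in a way that recorded NDI does not explain.

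In the upper-end case of 20% complete loss per arm with the shift in physiotherapy only, 3.3 points is enough to bring the upper limit from an observed difference of 0 to the margin. With 5% of the arm affected it takes 13.1 points. These figures assume SD 6, one outcome per patient and no precision gained from baseline or repeated measurements. A smaller standard error would leave more room and raise the shift needed.

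The stronger reading, that up to 20% missing patients will hide inferiority, is not supported: it would need the shift to differ between arms, and nothing in the document shows that.

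**What to change.** In section 2.3.4, use the existing two-week call to complete the NDI by phone with a fixed script, and record that the mode was telephone. In the same section, state that questionnaires continue after treatment is stopped, cancelled or switched, unless consent is withdrawn.

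The cost is a few minutes within a call already planned, with no extra staff or visits. The downsides are a possible phone-versus-online mode effect, which the flag allows to be examined, and a slightly late assessment for those patients. Recruitment began in May 2024 and data collection is expected to run to July 2027, so only assessments still to come would benefit; that favours an early change.

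As a supporting step, confirm that the full plan contains one delta-shift analysis of the primary contrast. It would impute all randomised patients, raise the missing physiotherapy NDI in steps, and report the shift at which the upper limit crosses 3 points. This costs one additional analysis.

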#### Cost-effectiveness analyses

2.9.3

The economic evaluations will be performed for the primary effect measure ‘disability’ and QALYs. The Incremental Cost-Effectiveness Ratio (ICER) will be calculated by dividing the difference in costs across study arms by the corresponding difference in effects. These differences will be estimated using regression techniques that will account for one or more of the following statistical challenges: baseline imbalances, skewed costs and/or effects, correlated costs and effects, clustering of data and missing data, if applicable [58]. Incremental cost-effect pairs will be plotted on cost-effectiveness planes, and cost-effectiveness acceptability curves will be constructed. The latter indicate the probability of personalised multimodal physiotherapy being cost-effective in comparison to surgery for various values of willingness to pay (i.e., the maximum amount that decision-makers are willing to pay per unit of effect gained). Sensitivity analyses will be performed to assess the robustness of the results (e.g., complete-case analysis and per protocol).

#### Process evaluation

2.9.4

Descriptive statistics will be used to analyse the quantitative part, and a thematic content analysis for the qualitative part (i.e., mixed-methods design).

### Patient and public involvement

2.10

A panel of four people with painful CR co-developed the study design, research questions, choice of treatment groups, and patient burden. Two of these people and two representatives from the public reviewed the patient information letter, and their feedback was used to further improve the letter.

### Data, integrity, and management

2.11

A data management plan is set up to ensure findable, accessible, interoperable, and reusable (FAIR) use of data [59]. Collected data consist of signed informed consent, digitally provided information, and physical test reports (either online or on paper). All data will be de-identified using a unique participant number. The data obtained from the samples are exported directly to a research drive only accessible to employees of the research team at the Vrije Universiteit Amsterdam. To ensure data quality, data constraints are pre-programmed in the online questionnaire. Further, frequent checks of coherent reporting are conducted. Clinical investigators assessing outcomes are trained to conduct the test in a standardised way and use a fixed protocol.

### Ethics and dissemination

2.12

The study will be conducted according to the principles of the Declaration of Helsinki (2013) and the Medical Research Involving Human Subjects Act (WMO). The research team will process the data, and both positive and negative findings will be disclosed unreservedly. Results will be submitted for publication to peer-reviewed scientific journals. Individual de-identified participant data that underlie the results will be shared. Investigators whose proposed data use has been approved may access the data for individual participant data meta-analysis.

The study is approved by the Medical Ethics Committee (METC) Brabant which can be found under the reference number P2327 and is preregistered at the Open Science Framework (OSF) under S7HWA (https://doi.org/10.17605/OSF.IO/S7HWA) at June 27th, 2023. In case of important protocol changes an amendment will be submitted for approval to the METC Brabant.

## Discussion

3

This paper describes the protocol for a non-inferiority randomised clinical trial that will assess the (cost-)effectiveness of personalised multimodal physiotherapy compared to ACDF surgery over a 12-month period in patients with painful CR who have an indication for surgery. We hypothesise that personalised multimodal physiotherapy is non-inferior to ACDF surgery in patients with painful CR based on disability over one year.

There is a strong need for studies investigating the effectiveness of personalised multimodal physiotherapy [14]. To our knowledge, this is the first study that simultaneously investigates the effectiveness and cost-effectiveness of personalised multimodal physiotherapy compared to surgery in patients with painful CR who have an indication for surgery. The personalised multimodal physiotherapy treatment is unique and carefully developed based on prior research into the effectiveness of the interventions for painful CR [[60], [61], [62]]. We believe the design of this study allows to assess whether the proposed treatment is a feasible alternative to ACDF surgery, which is the golden standard for painful CR and generally regarded as effective in reducing pain associated with this condition [12,13,[63], [64], [65]]. The non-inferiority design allows for flexibility in the treatment choice for people with painful CR, by demonstrating that personalised multimodal physiotherapy might be comparable effective on disability whilst offering additional benefits that might align better with individual preferences.

Besides the strengths, the proposed study has some potential limitations. The use of a non-inferiority margin is inherently prone to discussion. When comparing conservative treatment to no-treatment, the between-group difference should be at least 20% [50]. In this study, however, we compare conservative treatment to surgical treatment. As surgery is an invasive treatment associated with higher risks for (serious) adverse events, and based on the smallest worthwhile effect for chronic sciatica complaints [52], we increased the threshold to 30%. This results in a non-inferiority margin of 3 points on the NDI. Further, the use of the NDI as primary outcome measure doesn't take into account the radicular arm pain, which is one of the most important symptoms people with painful CR experience [12,23].

The results of this study will contribute to a better understanding of (cost-)effectiveness of personalised multimodal physiotherapy for painful cervical radiculopathy, and might offer a good alternative treatment option to surgery. Depending on the findings, multifaceted implementation strategies will be developed (e.g., educational) to facilitate implementation at different levels (e.g., healthcare professionals and guidelines).

## Data Availability

No data was used for the research described in the article.
